### Data Collection

#### Baseline Assessment

Baseline assessments include demographic data and Ayurveda parameters. It also includes assessing BERA, TFI, and MoCA score (Table 1).

#### Treatment Logs

For BTHE and TOPMAC intervention sessions, the drug compliance reports will record the date, clinician details, day of intervention, mode of delivery, and drugs issued.

#### Follow-Up Assessment

All participants will attend on day 29, day 57, day 85, day 113, day 141, and day 169 for follow-up. Drug compliance (%), concomitant medication, and rescue medication will be assessed at all visits. In addition to that, PTA, BERA, laboratory investigations, TFI, and MoCA score will be repeated on day 85 and day 169 (Table 1).

### Early Discontinuation/Withdrawal of Participants

During the study, participants can withdraw at any time. Moreover, the investigator may discontinue a participant from the study if they judge it indispensable for any reason, that is, if the patient is not ready to continue or is noncompliant with the study procedure (at least 80% compliance is crucial to continue in the study); if the patient develops a life-threatening crisis or any other severe sickness due to other pathology, which requires emergency treatment or making it necessary to introduce new treatment during the study period; or if the patient experiences any adverse event or adverse reaction requiring hospitalization. The decision to withdraw a participant from the study will be made only by the investigator, who will provide a thorough justification and indicate further management if needed. The sponsor and the ethics committee will be informed within 2 working days.

### Data Management

Data would be collected using paper case record forms (CRFs) and electronic CRFs and maintained by the principal investigator. Regularly monitoring data entry and data collection processes will be executed during the project. The electronic CRF for data entry will also be used to check data accuracy and validity. The modeling imputation technique will impute any outlier or missing data. The parameters having follow-ups will be imputed through the time series modeling, and those with single-point observations will be imputed with the population’s average or median depending on the variable’s distribution. The data will be collected and entered in the CRFs identified by the enrollment IDs only. The consent document and the screening and baseline information containing the participants’ names or identities will be secured more cautiously. The electronic format will be locked by password, and access to this data set will be restricted to authorized persons only. The shared data file will be locked with a separate code that can be accessed after the code is disclosed on request. The statistician at the CCRAS headquarters will analyze the data. After completion of the study, the data will be stored for at least 5 years.

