### Primary Outcomes

The primary outcomes include differences in the average 500 Hz, 1 kHz, and 2 kHz in PTA from baseline and after the 24th week of intervention. PTA is the gold standard for measuring sensitivity and identifying the presence and degree of hearing loss. PTA (isolated frequency) over a range of frequencies critical for everyday listening can determine the degree, configuration, and type of hearing loss in a manner detailed enough to assist the health care team in determining the etiology and prognosis for the hearing loss as well as the optimal treatment strategy [24]. Pure-tone evaluation is typically performed in a sound-treated booth to reduce the impact of external sounds, with the booth environment and electroacoustic equipment calibrated to American National Standards Institute standards to optimize intertest and intratest reliability. Primary outcomes also include Brainstem Evoked Response Audiometry (BERA) changes and differences in speech recognition threshold and speech discrimination score.

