### Sample Size Determination

A previously published report on the administration of topical oil pooling in patients with presbycusis showed that the average hearing level for the frequency of 500 Hz, 1 kHz, and 2 kHz after treatment was 53 dB (for air conduction defect of the right and left ears) [11]. We based our sample size calculation on the assumption that the average hearing level at these 3 frequencies will be 50 dB in the TOPMAC+BTHE group, while it will be 60 dB in the BTHE group. A difference of 10 dB after treatment between both groups has been considered clinically meaningful. With a standard deviation of 12 dB, 80% power, and a confidence interval of 95%, the calculated sample size for each arm is 23. The sample size becomes 28.75, rounded to 30 per arm, adding an attrition rate of 25%. Therefore, 60 participants must be enrolled in the trial (30 in each arm). The attrition rate was based on the clinical experience in treatment compliance. Moreover, in a previous study [25] on Ayurveda interventions among older participants, such attrition had occurred. An interim analysis will be performed after 25% of the participants complete the study duration, and then the reassessment of the attrition rate will be considered along with the original sample size.

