### Statistical Methods

Data will be managed through SPSS software (version 29.0; IBM Corp). The data would be individually analyzed for central tendencies (mean, median), range, standard error, standard deviation, and 95% CIs for each intervention arm in each of the groups in the study. Data will be tabulated and graphically shown using a standard format, Microsoft Excel, and other software programs. For nonparametric values, the Wilcoxon signed-rank test and Mann-Whitney *U* test will be performed, and for parametric values, a paired 2-sided *t* test and Student *t* test will be done. Further, multivariable regression and Cox regression analyses will be used if any confounding factor or censored data are found during the analysis. Bayesian analysis may also be performed if any necessity arises after the initial phase of data analysis. This study will assess patients with mild to moderate presbycusis based on impairment. Clinically, it is established that participants with moderate impairment have a lesser chance of cure and persons with mild impairment have a higher chance of cure, which is the available information before the study starts. Therefore, we use this information as prior distribution to calculate the later treatment response of the participants. Further, Bayesian analysis gives another angle to explore the outcome and reduce the researcher’s dependency on *P* values.

Regression analysis will control the diversity during analysis and stratify results by demographic factors such as sex, socioeconomic status, and comorbidities. The analysis will be done by stratifying these factors to estimate the effect of the intervention as accurately as possible. The regression analysis will consider these factors to determine the intervention’s adjusted effect. In the case of dichotomous or multinomial type of data, a separate analysis will be performed for each stratum, or logistic regression analysis will be used.

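### The plan imputes any outlier, so genuine audiometry can be overwritten; it also fills missing outcomes by time series modelling on at most three visits, with no stated allowance for imputation uncertainty

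*Protocol article*

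**What the plan says.** The rule is in Data Management: "The modeling imputation technique will impute any outlier or missing data". It is then split by type of variable. For repeated measures, "The parameters having follow-ups will be imputed through the time series modeling". For the others, "those with single-point observations will be imputed with the population’s average or median", depending on the distribution.

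The primary outcome is a repeated measure: "differences in the average 500 Hz, 1 kHz, and 2 kHz in PTA from baseline and after the 24th week of intervention". Follow-Up Assessment gives its schedule: "PTA, BERA, laboratory investigations, TFI, and MoCA score will be repeated on day 85 and day 169". With the screening or baseline value, each participant has at most three readings.

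Statistical Methods names the tests: "for parametric values, a paired 2-sided *t* test and Student *t* test will be done", with Wilcoxon and Mann-Whitney tests for nonparametric values. It mentions no step that carries imputation uncertainty into these tests. Sample Size Determination plans for substantial loss, "adding an attrition rate of 25" percent. The section on randomization and blinding says that the statistician is not blinded to allocation.

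**The concern.** There are two separate issues.

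**Outliers.** An observed value is replaced because it is extreme, not because it is wrong. In a trial of change in hearing, the extreme values include the best responders and the worst deteriorations, which are what the trial is meant to measure. Replacing them with something nearer the centre shrinks the standard deviation and so the standard error. Because no threshold is given and the analyst knows the arms, the rule also leaves room for choices that depend on the result.

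**Missing values.** Two or three readings per person give a time series model very little to work with. If the completed data go into a t test as though all were observed, the test may count participants who supplied no Day 169 reading as full information. With a quarter of participants expected to leave, this could affect the primary comparison materially.

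**Working it through.** **Inputs from the protocol article.** SD 12 dB, difference 10 dB, 80% power, 95% confidence, 23 per arm evaluable, 25% attrition, 30 per arm enrolled (Sample Size Determination); visits at screening or baseline, Day 85 and Day 169 (Table 1, Follow-Up Assessment).

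**Assumptions, because the document gives no figure.** The outlier threshold, the imputation model, the correlations between visits (baseline to Day 169 varied from 0.5 to 0.9), and values missing completely at random.

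**Step 1: the plan's own figure.** n = 2(1.96 + 0.84)² × 12² / 10² = 22.6, so 23 per arm, as stated. Inflation: 23 × 1.25 = 28.75, rounded to 30. With 23 observed per arm and no imputation, simulation gave a mean SE of 3.51 dB, type I error 4.9% and power 79%. This is the benchmark.

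**Step 2: outlier replacement alone, no missing data, no true effect, 30 per arm.**

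| Assumed rule | Type I error |
|---|---|
| Beyond 2 SD, set to arm mean | 11-12% |
| Beyond 1.5 IQR, set to median | 8-9% |

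The mechanism shows in one 2 SD run. With nothing replaced, the true SE is 12 × √(2/30) = 3.10 dB. After replacement the reported SE fell to 2.70 dB, while the actual spread of the estimate rose to 3.43 dB, a ratio of 0.79. The implied error is 2[1 − Φ(1.96 × 0.79)] ≈ 12%, matching the simulation. Every replaced value was genuine.

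**Step 3: missing Day 169 values filled once, t test on change, no true effect.** There were 7 or 8 of 30 missing per arm.

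| Fill | Type I error |
|---|---|
| Arm mean | about 8% |
| Regression on baseline, fitted within arm | 11-13% |
| Regression on baseline and Day 85, fitted within arm | 9-11% |
| Last value carried forward | about 5% |
| Straight-line extrapolation | about 5% |
| Mean or regression pooled over arms | about 5% |
| Observed values only | about 5% |

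For the within-arm regressions the reported SE was 78-85% of the true SE. As a check, 2[1 − Φ(1.96 × 0.78)] ≈ 13% and 2[1 − Φ(1.96 × 0.85)] ≈ 10%.

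**Step 4: the other possible harm.** A mean pooled over arms keeps type I error near 5% but gives the missing participants in both arms the same value. With 23 of 30 observed, a true 10 dB difference becomes 10 × 23/30 = 7.7 dB; simulation agreed. For comparison, Sample Size Determination says: "A difference of 10 dB after treatment between both groups has been considered clinically meaningful".

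**The case against.** **The outlier sentence may only mean data cleaning.** It follows a sentence on using the electronic record form to check accuracy and validity. That reading is plausible, but the text does not make imputation depend on a failed check, and nothing elsewhere limits the word *any*. It is also true that the 2 SD and 1.5-IQR rules are assumed, so the 8-12% illustrates the effect rather than predicting it.

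**Single imputation is not stated.** A reader might infer that the plan uses single imputation and that its standard errors are therefore too small. The document does not support this as fact. It names time series modelling without saying how many imputations are made or how they are pooled, and an article may leave that to a fuller document. Straight-line extrapolation and last value carried forward, arguably the nearest simple analogues, showed no inflation. This objection stands, so the claim about false positives has to be conditional on the model.

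**Mean filling does not apply to the outcomes.** A reader might apply the mean or median fill to audiometry. The plan reserves it for single-point variables, which in Table 1 are demographics and tympanometry, and it refers to the population's average, not the arm's. The arm-mean row above is therefore illustrative only.

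**One in four is a planning ceiling.** The 25% is an allowance that is to be reassessed at the interim analysis. The plan does not say whether withdrawn participants, as opposed to sporadic gaps, would be imputed.

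**The trial is exploratory.** It is, but a positive result is intended to steer a definitive trial, so the label does not make altered primary data harmless.

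**Conclusion.** The outlier half holds on the text. As written, the rule permits genuine primary-outcome values to be overwritten, with no definition and no test of error. Its size is a type I error of about 8-12% instead of 5%, given 30 per arm, normally distributed values and the assumed thresholds.

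The missing-data half holds in a conditional form. Time series modelling on at most three visits, followed by ordinary tests with no stated allowance for imputation uncertainty, is a poor choice when 25% attrition is expected. If the fills are single predictions treated as observed, type I error ranges from about 5% to about 13% depending on the model. One of the fills that leaves it near 5%, the mean pooled over arms, costs about 23% of a true effect (10 dB to 7.7 dB). The document does not show which of these would occur, so a flat statement that the standard errors will be too small is not supported.

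**What to change.** 1. Delete the imputation of outliers. Query extreme values against source, correct only verified errors, and keep every other observed value. Report a rank-based analysis of the primary outcome as a sensitivity analysis; the plan already names Mann-Whitney and Wilcoxon tests.
2. For pure tone average, BERA, TFI and MoCA, replace time series imputation with a repeated-measures mixed model on all observed baseline, Day 85 and Day 169 data. Multiple imputation with Rubin's rules is an acceptable alternative.

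The cost is a change of wording and slightly more programming. Confidence intervals may be wider, which reflects the information actually collected. No visit or measurement changes. The article reports 22 participants enrolled as of August 2024 and analysis not yet begun; if that is still so, the change can be made before any outcome data are analysed.

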### Statistical Methods

Data will be managed through SPSS software (version 29.0; IBM Corp). The data would be individually analyzed for central tendencies (mean, median), range, standard error, standard deviation, and 95% CIs for each intervention arm in each of the groups in the study. Data will be tabulated and graphically shown using a standard format, Microsoft Excel, and other software programs. For nonparametric values, the Wilcoxon signed-rank test and Mann-Whitney *U* test will be performed, and for parametric values, a paired 2-sided *t* test and Student *t* test will be done. Further, multivariable regression and Cox regression analyses will be used if any confounding factor or censored data are found during the analysis. Bayesian analysis may also be performed if any necessity arises after the initial phase of data analysis. This study will assess patients with mild to moderate presbycusis based on impairment. Clinically, it is established that participants with moderate impairment have a lesser chance of cure and persons with mild impairment have a higher chance of cure, which is the available information before the study starts. Therefore, we use this information as prior distribution to calculate the later treatment response of the participants. Further, Bayesian analysis gives another angle to explore the outcome and reduce the researcher’s dependency on *P* values.

Regression analysis will control the diversity during analysis and stratify results by demographic factors such as sex, socioeconomic status, and comorbidities. The analysis will be done by stratifying these factors to estimate the effect of the intervention as accurately as possible. The regression analysis will consider these factors to determine the intervention’s adjusted effect. In the case of dichotomous or multinomial type of data, a separate analysis will be performed for each stratum, or logistic regression analysis will be used.

### Data Monitoring

This study will be monitored by the Data and Safety Monitoring Board of the TOPMAC project at NARIP, Cheruthuruthy. A particular quality control program would be initiated to secure an agreement with the present approved protocol, good clinical practice, related regulations, and SOPs of NARIP. The principal investigator will develop data management and monitoring plans and manage the trial’s daily activities. The Data and Safety Monitoring Board team will perform quality assurance checks to ensure the integrity of randomization, study entry procedures, and data collection. The Data and Safety Monitoring Board team will conduct at least one e-Clinical Research Form inspection once a year. Additionally, the sponsor may monitor or audit the study per the approved protocol, good clinical practice, relevant regulations, and SOPs.

### Ethics Approval and Dissemination

The institutional ethics committees at NARIP (3/1/2020/NARIP/Tech/2036 dated January 31, 2023) and ICCONS (IEC006 dated March 21, 2023) approved this study (protocol-1 dated February 3, 2023). This study was registered on April 11, 2023 (CTRI/2023/04/051485). This protocol is reported according to the SPIRIT (Standard Protocol Items: Recommendations for Interventional Trials) statement [26] (completed SPIRIT checklist: Multimedia Appendix 1). Results would be published in a peer-reviewed journal with authorship eligibility according to the criteria of the International Committee of Medical Journal Editors.

## Results

This project was funded in January 2023. The institutional ethics committees at NARIP (3/1/2020/NARIP/Tech/2036 dated January 31, 2023) and ICCONS (IEC006 dated March 21, 2023) approved this study. The first patient was enrolled in September 2023; 22 participants were enrolled as of August 2024. The data analysis is yet to start, and the results are expected to be published by January 2025.

## Discussion

This randomized exploratory trial is proposed to assess the efficacy of TOPMAC intervention in improving the hearing status of adults aged 60-75 years with mild to moderate presbycusis.

### Strength

The TOPMAC intervention was methodically developed, amalgamating existing best and anecdotal shreds of evidence, and is the first trial to evaluate the effectiveness of Ayurveda intervention in presbycusis as an add-on to BTHE. The quantitative outcome measures included in this trial will give valid data about the possibility of performing a definitive randomized controlled trial of the TOPMAC intervention.

### Limitations

This study has limitations, as only effectiveness outcomes are included and not feasibility outcomes. This trial design has no follow-up period. The lasting effects of the treatment on presbycusis and associated symptoms may need to be assessed. Nevertheless, a case study has been reported, wherein the treatment effect of Ayurvedic medicines in presbycusis was sustained for a follow-up period of 6 months when no treatment was administered [23]. This study will apply only to Asian countries where Ayurveda is practiced. Nonetheless, the applicability of this protocol is limited in other continents. However, they could also replicate this model if there is accessibility of trained Panchakarma therapists to perform the Karnapurana procedure and if they have regulatory permissions to use Ashwagandha.

Another limitation is the absence of subjective Ayurvedic diagnostics in the research design, which might influence the broader integration of Ayurvedic treatments into conventional medical practice. However, Badhirya and Karnanada are described in Ayurveda and can be correlated with various symptoms of presbycusis. Although the standardized or validated assessment criteria for severity are not available in Ayurveda terminology, the outcome measures/tools for the assessment of presbycusis are conceptually applicable to inferring the results for Badhirya. Further, this protocol evaluates the patient’s prakriti (psychosomatic constitution) by using the standardized Ayur Prakriti web portal developed by CCRAS [27]. Prakriti is considered an essential part of Ayurvedic diagnostics [28]. Although TFI is a robust tool for assessing tinnitus impact, the absence of a broader quality of life measure for other dimensions possibly affected by the treatment is yet another limitation of this protocol. These limitations will be considered in the future definitive randomized controlled trial.

### Conclusion

If this exploratory trial is proven effective, it will steer the setting of a definitive randomized controlled trial, which will incorporate the limitations as described above, to test whether the TOPMAC intervention can be incorporated as a cost-effective integrative approach for managing presbycusis.

## Appendix

Multimedia Appendix 1 SPIRIT (Standard Protocol Items: Recommendations for Interventional Trials) checklist.

## Abbreviations

BERA: Brainstem Evoked Response Audiometry
BTHE: basic treatment and health education
CCRAS: Central Council for Research in Ayurvedic Sciences
CRF: case record form
ICCONS: Institute for Communicative and Cognitive Neuro Sciences
MoCA: Montreal Cognitive Assessment
NARIP: National Ayurveda Research Institute for Panchakarma
PTA: pure tone audiometry
SOP: standard operating procedure
SPIRIT: Standard Protocol Items: Recommendations for Interventional Trials
TOPMAC: Topical Oil Pooling with Kshirabala Taila and Supplementation of Ashwagandha Churna
